### Plans to promote participant retention and complete follow-up {18b}

Every 2 weeks, participants will get an invitation to fill in some questions regarding the PU incidence and the intervention group will also be asked to complete the diary. When opening the online questionnaire, an overview is visible showing which questionnaire has already been completed and which questionnaire has not yet been completed. When a questionnaire is not fully completed or submitted a week after the invitation, the local researcher of Reade will contact the participant.

### Data management {19}

All data collected during this trial will be coded and de-identified and, if possible, anonymized/pseudonymized to protect the privacy of our participants and to allow open access publication of our data after the completion of the trial on the basis of the FAIR principles (69). During the course of the trial, data storage will be controlled by the PI (TJ) and the executive researcher (BW). All physically collected data (e.g. screenings forms and informed consent) will be stored in a secure locker with restricted access. All other collected data will be stored directly on Research Drive (SURF, Utrecht, The Netherlands).

The paper-based screening forms and informed consent forms will be filed by the local research assistant of the participating centres. He/she will scan all forms and upload them to Research Drive, after which he/she will collect some additional information to complete the Case Report Form (CRF). Data will be stored and managed in accordance with the quality standards of the VU Amsterdam, the Netherlands. All data collections, changes and interpretations will be documented in a codebook, which will be saved on Research Drive as well. This will be done for review and reuse purposes. Physical measurement data will be processed using Matlab and ImageJ, after which the data will be imported to SPSS. Statistical analyses will be done in SPSS, STATA and R. Throughout the data cleaning process, every step will be documented and in the scripts/syntaxes. When students will get involved in data collection/cleaning process, a short protocol will be made. A more detailed Data Management Plan (DMP) is written for this trial and available Appendix 3.

### Confidentiality {27}

The outcome data will be separately stored from the participant-identifying information and participants will be coded with a unique study ID. The personal information will only be accessible for the local researcher of the rehabilitation centre, the principal investigator and executive investigator. Rights of access will be strictly regulated by the executive researcher (BW).

### Plans for collection, laboratory evaluation and storage of biological specimens for genetic or molecular analysis in this trial/future use {33}

Not applicable, no samples collected.

### Statistical methods for primary and secondary outcomes {20a}, {20c}

Descriptive statistics will be used to describe the participants’ baseline characteristics: age, gender, level of SCI, ASIA score, time since injury, number of previous PUs. Potential confounders will be identified by adding them to the regression equations and checking whether they change the regression coefficient by more than 10% or based on the literature. If there are any clinically relevant differences between groups at baseline, we will include these potential confounders in the analysis.

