## Assignment of interventions: allocation

### Implementation {16c}

#### Sequence generation {16a}

Randomization will be done by the research assistant of Reade. Participants will be randomly assigned to either the intervention or control group in a 1:1 ratio with a web-based randomization program (studyrandomizer.com). A permuted block algorithm will be used with a variable block size with a minimum of 4, a maximum of 8 and an increment of 2. Randomization will be stratified for rehabilitation centre and for two age groups; i.e. 18–70 years and ≥70 years. Randomization list will only be available to the local researcher of the rehabilitation centre, the executive investigator and principal investigator. The research assistant of Reade is also the one who completes the Case Report Form (CRF) and keeps everyone posted on how many participants are enrolled to the study.

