#### Baseline characteristics

At baseline, the following determinants, which can have an effect on developing PUs and are potential confounders, are also collected: age, sex, cause of SCI, level of SCI, Asia Impairment Scale, time since injury, rehabilitation centre, number of PUs in the past, locations of PUs in the past, PU surgery in the past (yes/no and how often), type of surgery, comorbidities (heart and vascular, stomach liver, intestinal or kidney disease, bladder, urinary or respiratory problems, diabetes, history with cancer, musculoskeletal or other neurological disorders) and spasms (yes/no and if yes, which muscles).

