#### Effect analysis

An intention-to-treat analysis will be performed using a logistic mixed model with having had a PU during 12-month follow-up (yes/no) as a dependent variable and as independent variables the study group variable (intervention or usual care group) and any potential confounding variables. Two levels will be identified; i.e. rehabilitation centre and patient. The necessity of using a random intercept and/or a random slope will be assessed using the -2 log likelihood test. If both turn out not to be necessary, a regular logistic regression analysis will be performed. Also, as maximum likelihood estimation cannot be used to deal with missing data in these analyses, missing data will be multiple imputed using Multivariate Imputation by Chained Equations (MICE) and pooled estimates will be calculated using Rubin’s rules [57].

An intention-to-treat analysis will also be performed for the secondary outcomes using a linear mixed model for continuous outcomes (e.g. quality of life). Three levels will be identified: i.e. rehabilitation centre, patient and time. Within these models, the secondary outcomes will serve as the dependent variable, a study group variable (intervention or usual care group), interaction terms for study group and time and all confounding variables will be the independent variables. Again, the necessity of using a random intercept and/or a random slope will be assessed using the -2 log likelihood test.

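### The 10% change-in-coefficient rule lets the treatment estimate help choose its own primary model and modestly inflates the type I error

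*Protocol article*

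**What the plan says.** The section on statistical methods for primary and secondary outcomes gives two routes by which a variable becomes a confounder: "Potential confounders will be identified by adding them to the regression equations and checking whether they change the regression coefficient by more than 10" per cent, "or based on the literature". No variable is named under the literature route. The section then adds: "If there are any clinically relevant differences between groups at baseline, we will include these potential confounders in the analysis". No threshold for such a difference is given.

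The Effect analysis section passes the result to the primary model. The outcome is "having had a PU during 12-month follow-up (yes/no) as a dependent variable", with "as independent variables the study group variable (intervention or usual care group) and any potential confounding variables". The linear mixed models for secondary outcomes take up the confounders in the same way.

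The candidate pool is left open. The statistical section lists six baseline variables, for description only: age, gender, level of injury, ASIA score, time since injury and number of previous pressure ulcers. The Baseline characteristics section lists 13 and labels them "determinants, which can have an effect on developing PUs and are potential confounders". One of the 13 is rehabilitation centre, which the primary model already treats as a level.

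**The concern.** Allocation is random: "Participants will be randomly assigned to either the intervention or control group in a 1:1 ratio". Baseline differences are therefore chance, and the adjustment set need not be learned from the outcome data. The 10% rule learns it from the quantity under test, for three reasons a poor guide:

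- **Non-collapsibility.** Adding a prognostic covariate to a logistic model shifts the treatment odds ratio even when the arms are perfectly balanced, so a 10% shift is not evidence of confounding.
- **A threshold that shrinks with the effect.** If the treatment coefficient is small, 10% of it is trivial and pure noise passes.
- **Unacknowledged selection.** The reported p-value and interval treat the final model as if it had been fixed in advance.

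At stake are the error rate of the primary test and whether its model is determined before the data are seen.

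**Working it through.** The protocol states no type I error for this procedure beyond alpha 0.05 in the sample size section, so there is no figure to reproduce. Sidedness is not stated there; two-sided 5% is assumed here.

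**Inputs from the protocol.** 45 analysable participants per arm, 35% versus 10% (Sample size); binary endpoint and logistic model (Effect analysis); six or 13 candidates, or 12 without centre.

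**Expected events.** 45 × 0.35 + 45 × 0.10 = 15.75 + 4.5 = 20.25.

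**Why noise passes near the null.** With the average rate of 22.5% in both arms, each arm expects 10.125 events and 34.875 non-events.

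- SE of the log odds ratio: √[2 × (1/10.125 + 1/34.875)] = √0.2549 = 0.505.
- Median absolute estimate under no effect: 0.6745 × 0.505 = 0.341.
- 10% of that is 0.034, or about 0.07 of one standard error.

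At the design effect the log odds ratio is ln(0.10/0.90) − ln(0.35/0.65) = −2.197 + 0.619 = −1.578. There the threshold is 0.158, over four times as large.

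**Simulation under no effect.** 45 per arm, ordinary logistic regression, 3,000 to 5,000 runs per scenario, Monte Carlo error about ±0.6 to 0.8 points. Assumptions not in the protocol: independent covariates, no centre effect, no missing data, the prognostic strengths shown (log odds ratio per SD), and an imbalance threshold of a standardised difference above 0.3. The forward version was capped at eight covariates. The fixed set held three covariates, prognostic ones where the scenario had any.

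Rejection rates (%), Wald test:

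| Candidates; event rate | Unadjusted | 10% rule, one at a time | 10% rule, forward | Imbalance rule alone | Either rule | Fixed set |
|---|---|---|---|---|---|---|
| 6 noise; 35% | 4.3 | 5.4 | 5.5 | 4.2 | 4.9 | 4.8 |
| 6, three prognostic (0.5); 35% | 4.6 | 6.8 | 7.2 | 4.4 | 6.3 | 5.4 |
| 6, three prognostic (1.0); 35% | 5.0 | 6.7 | 8.1 | 3.5 | 6.2 | 5.4 |
| 6, all prognostic (0.4); 35% | 4.4 | 6.6 | 7.5 | 3.9 | 6.3 | 4.7 |
| 13 noise; 35% | 4.8 | 7.2 | 7.7 | 4.8 | 6.4 | 5.2 |
| 13 noise; 22.5% | 4.4 | 6.8 | 7.7 | 4.8 | 5.9 | 4.5 |
| 13, three prognostic (0.5); 22.5% | 5.0 | 8.3 | 10.4 | 4.7 | 7.2 | 5.6 |
| 13, six prognostic (0.4); 22.5% | 4.8 | 7.7 | 9.9 | 4.1 | 6.9 | 5.2 |

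Likelihood ratio tests run higher throughout: unadjusted 4.8–5.8%, fixed set 5.0–6.7%, 10% rule one at a time 6.0–9.7%, forward 6.1–12.1%, imbalance alone 4.0–5.9%.

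Other runs agree. With 12 noise candidates the one-at-a-time rule rejected in 7.0–7.6%, and with two prognostic covariates among them in 7.3–8.6%. With six candidates the other runs gave 5.2–6.4%.

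**How many noise variables enter.** Under no effect, 2.4 of 6 or 5.2–5.3 of 13 on average, with at least one in 85% and 94–95% of trials respectively. At 35% versus 10%, only 0.73 of 13 on average, with at least one in 44%.

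**Power of a fixed set.** At 35% versus 10% with three prognostic covariates (0.5), Wald power was 86.1% with the fixed set and 82.6% unadjusted.

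**The case against.** Several points on the other side carry weight.

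- **The text can be read as a gate.** The sentence on baseline differences may mean that candidates found by the 10% rule are included only if they also differ between arms. On that reading the rejection rate was about 4.5–6.5%, close to nominal. This stands, but the protocol does not settle which reading applies.
- **The pool may be small.** If only the six variables in the statistical section are candidates and all are noise, the rate is barely above 5%. This also stands, although the protocol itself labels 13 variables as potential confounders.
- **The literature route is legitimate.** It does not depend on the data. But it names no variable and sits beside the 10% rule as an alternative, so it does not displace it.
- **Covariate lists are commonly left to an analysis plan.** Their absence is indeed no finding. The point concerns the selection rule that the protocol does state.

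Two stronger readings are tempting and not supported. A reader might infer that adjusting for observed imbalance also inflates the error; alone it gave 3.5–4.8% in the table and at most 5.7% in other runs, so no material inflation. A reader might also set the roughly five noise variables beside the 20 expected events and conclude that the model will be badly overfitted if the design effect is real; that many enter only near the null.

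**Conclusion.** The concern holds for the 10% rule. It does not diagnose confounding in a randomised comparison, and it lets the treatment estimate influence its own model. At a nominal two-sided 5%, applied one covariate at a time and judged by the Wald test, type I error is about 5–6.5% with six candidates (6.8% at most) and about 7–9% with 12 or 13. Forward selection reaches 10.4%; the gate reading stays near nominal. These sizes rest on the simulation assumptions above and on taking the coefficient in the rule to be that of the study group, which the text does not spell out.

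The imbalance rule has a different fault: it is applied after seeing the data and has no threshold, so two analysts could reach different primary models.

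The inflation is modest and depends on how the text is read, so this should be fixed but does not by itself undermine the trial.

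**What to change.** Replace the selection text with a short covariate set named before unblinding: study group, age stratum (a randomisation factor that the model description does not name) and number of previous pressure ulcers. Remove the 10% rule and the imbalance rule from the primary analysis. Report the unadjusted result and any wider adjustment as sensitivity analyses.

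Keep centre as the random level already described in the Effect analysis section, not as dummy terms. Eight centres would add seven dummies to the three terms above, and 20.25 events over 10 slopes is about 2 per slope; with the three terms alone it is 20.25/3 = 6.75.

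The cost is one paragraph. All the variables are already collected, and under the assumed prognostic strength the fixed set lost no power. The downside is that a chance imbalance in an unlisted variable is handled only in a sensitivity analysis.

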#### Effect analysis

An intention-to-treat analysis will be performed using a logistic mixed model with having had a PU during 12-month follow-up (yes/no) as a dependent variable and as independent variables the study group variable (intervention or usual care group) and any potential confounding variables. Two levels will be identified; i.e. rehabilitation centre and patient. The necessity of using a random intercept and/or a random slope will be assessed using the -2 log likelihood test. If both turn out not to be necessary, a regular logistic regression analysis will be performed. Also, as maximum likelihood estimation cannot be used to deal with missing data in these analyses, missing data will be multiple imputed using Multivariate Imputation by Chained Equations (MICE) and pooled estimates will be calculated using Rubin’s rules [57].

An intention-to-treat analysis will also be performed for the secondary outcomes using a linear mixed model for continuous outcomes (e.g. quality of life). Three levels will be identified: i.e. rehabilitation centre, patient and time. Within these models, the secondary outcomes will serve as the dependent variable, a study group variable (intervention or usual care group), interaction terms for study group and time and all confounding variables will be the independent variables. Again, the necessity of using a random intercept and/or a random slope will be assessed using the -2 log likelihood test.

#### Economic evaluation

Cost-effectiveness analyses will be performed according to the intention-to-treat principle. Missing data will be imputed using Multivariate Imputation by Chained Equations (MICE) and pooled estimates will be calculated using Rubin’s rules [57]. Cost and effect differences will be estimated using linear mixed models or seemingly unrelated regression (SUR) analyses, depending on the number of required random intercepts and/or slopes [58]. Incremental cost-effectiveness ratios (ICERs) will be calculated by dividing the difference in costs by those in effects. BCa bootstrapping with 5000 replications will be used to estimate the uncertainty surrounding the ICERs and 95% confidence intervals around cost differences. Uncertainty will be shown by plotting cost-effectiveness planes and cost-effectiveness acceptability curves [59]. Sensitivity analyses will be performed to assess the robustness of the results (e.g. per-protocol analysis, complete-case analysis, human capital approach).

#### Process evaluation—mixed method analysis

Since both qualitative and quantitative data will be collected for the process evaluation, a mixed method analysis will be performed. Descriptive statistics (mean, SD, proportions) will be used to report the participants’ results of the closed questions and collected diary data. The open questions of the questionnaire will be listed, analysed and summarized. The main researcher (BW) and the implementation specialist (FvN) will code transcripts and other data qualitative obtained during the study. A framework analysis approach will be used to identify barriers and facilitators for adoption, implementation and maintenance [38]. Because both qualitative and quantitative data will be collected during the study, data triangulation will be used for the analysis. During this process, the researchers are mainly looking for outstanding differences or contrasts. Whether the data can support or supplement each other will also be looked into. To investigate the effect difference between different adherence groups within the intervention group, the group will be split in a low and high adherence group. A regression analysis will be performed to analyse the difference between these groups. Conclusions and claims shall be made carefully because of the between-study differences and explanation of heterogeneity [38]. To visualize the effect, a dose-response curve will be made.

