#### Relevance

After being diagnosed with a PU, treatment can either be conservative or surgical (debridement) and reconstructive and very often consists of mandatory prolonged bed rest to release pressure on the wound(s). Even though bed rest alleviates pressure on the wound, it also has some severe negative consequences, such as decreased mobility and independence and reduced physical condition, health-related quality of life and level of participation. On top of that, PUs are associated with high societal costs due to increased health care utilization and work absenteeism [2, 3, 23]. Consequently, preventing the recurrence of PUs will likely lead to a reduction of the burden to individuals with SCI and society.

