##### Process evaluation

Parallel to the RCT, a mixed methods process evaluation will be conducted using the RE-AIM model [59]. The aims of the process evaluation are (1) to evaluate recruitment, reach and implementation of the daily ES, and participants’, care takers’ and key stakeholders’ experiences of taking part in daily ES to explain program outcomes, including unintended outcomes; (2) to evaluate the views of rehabilitation specialist on the usage of ES as a rehabilitation method; (3) to investigate facilitators and barriers for the adoption, implementation and maintenance of daily ES of gluteal and hamstring muscles combined with usual care; (4) to explore dose-response association between the degree of adherence and effectiveness; (5) to provide recommendations for improvement of the intervention beyond the research setting. The mixed-method design of this process evaluation will include interviews with; the participant, caregivers and specialist. Focus groups with a rehabilitation specialist, researchers, nurse practitioners coordinators and managers, field notes and a question included in the ES questionnaire and diary [60, 61]. Interviews will be held at T1 and after T3, focus group at T3, while questionnaire and diary data will be collected throughout the trial. For further details, see Appendix 1.

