### Methods for additional analyses (e.g. subgroup analyses) {20b}

Depending on the course and outcomes of this study, additional sub-group analyses might be performed, e.g. between the different ASIA scores, how often someone has a PU, if someone has a PU during different times during the study, adherence to the intervention and the grade and location of the PU. The association between all risk factors and PU development/ incidence will also be looked at.

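### The low/high adherence comparison and dose-response curve do not limit adherence to ES use before the first pressure ulcer, so reverse causation could produce an apparent dose-response

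*Protocol article*

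**What the plan says.** Aim 4 of the process evaluation (Protocol article, Process evaluation) is "to explore dose-response association between the degree of adherence and effectiveness". The analysis is given under Process evaluation—mixed method analysis: within the intervention arm "the group will be split in a low and high adherence group". Then: "A regression analysis will be performed to analyse the difference between these groups". And: "To visualize the effect, a dose-response curve will be made". The article gives no cut-off, no time window for adherence, and no outcome or covariates for this regression. The one caution reads: "Conclusions and claims shall be made carefully because of the between-study differences and explanation of heterogeneity".

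Other sections fix the timing. Under Effect analysis, the primary outcome is any PU during the 12 months, yes or no. ES is to be used for one year (Abstract, Methods). Use is tracked by diary twice a month (Usability and user-friendliness), and PU status is asked every two weeks (Primary outcome).

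Methods for additional analyses {20b} lists further analyses that might be done, including by "adherence to the intervention and the grade and location of the PU".

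**The concern.** Exposure and outcome share one 12-month window. If a PU leads a participant to use ES less afterwards, participants with a PU drift into the low-adherence group because of the outcome. Low adherers would then show more PUs than high adherers even if stimulation had no effect.

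The stated caution does not cover this. It refers to differences between studies, which does not fit a comparison within one arm of one trial, and it does not mention the direction of causation.

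Aim 4 would be affected, and so could aim 5 of the process evaluation, which is to recommend improvements to the intervention. A steep curve could be read as evidence of benefit even beside a null randomised comparison.

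**Working it through.** **Does the text make reduced ES use after a PU plausible?**
- Relevance: PU treatment very often involves long bed rest.
- Table 1 footnote: days of bed rest are recorded when a PU is reported, so the trial expects them.
- Criteria for discontinuing {11b}: skin irritation during ES calls for a temporary stop. A PU is not on that list.
- Intervention group: wounds on the back influence the choice between garment and electrodes.

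The mechanism is therefore plausible, but it is nowhere stated.

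**Inputs from the plan.** The plan gives no figure for the adherence analysis itself. Sample size {14} gives 45/0.9 = 50 per group, which reproduces, and PU risks of 35% (control) and 10% (ES). If ES does nothing, the ES arm carries the 35% risk. The 10% risk applies if ES works as planned but the amount of use does not matter.

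**Assumptions, not in the plan.** Personal adherence *a* follows a beta distribution with mean 0.75 and SD 0.15 (varied 0.10 to 0.25). It is unrelated to PU risk. PU time *t* is uniform over 52 weeks. There is no ES for *g* weeks after a PU. The arm is split at the median of 52-week adherence and tested with Fisher's exact test, 4,000 runs per setting.

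**Formula.** Measured adherence = a × (52 − L)/52, where L = min(g, 52 − t) after a PU and 0 otherwise. The mean loss is g − g²/104 weeks.
- g = 4: 4 − 16/104 = 3.85 weeks. 0.75 × 3.85/52 = 0.056, or 0.056/0.15 = 0.37 SD.
- g = 8: 8 − 64/104 = 7.38 weeks. 0.75 × 7.38/52 = 0.106, or 0.106/0.15 = 0.71 SD.

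A shift of this size in those with a PU is enough to move many of them across the median.

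**Results with no true effect (SD 0.15).** PU incidence in low vs high adherers; odds ratios (OR) are from the averaged proportions.

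| Weeks off | 35% risk: low vs high | OR | p<0.05 | 10% risk: low vs high | OR | p<0.05 |
|---|---|---|---|---|---|---|
| 0 | 35.0% vs 34.7% | 1.01 | 2.5% | 10.1% vs 10.0% | 1.01 | 1.1% |
| 2 | 38.3% vs 31.4% | 1.35 | 4.5% | 11.4% vs 8.5% | 1.38 | 1.3% |
| 4 | 42.1% vs 28.2% | 1.85 | 10.7% | 12.9% vs 7.1% | 1.93 | 2.9% |
| 8 | 48.9% vs 20.9% | 3.61 | 45.2% | 16.0% vs 4.1% | 4.52 | 10.9% |
| 12 | 55.4% vs 14.6% | 7.26 | 81.7% | 18.3% vs 1.8% | 11.87 | 24.0% |

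**Sensitivity.** At 35% risk and 8 weeks off, SD 0.25 gives OR 2.40 (p<0.05 in 23% of runs) and SD 0.10 gives OR 6.77 (79%). A second model, with adherence normal with mean 0.7 and SD 0.2 truncated to 0–1, gives at 10% risk:
- 0 weeks off: 10.2% vs 10.0%
- 4 weeks off: 11.9% vs 8.0%
- 8 weeks off: 14.0% vs 6.2%

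At 35% risk and 8 weeks off it gives 45% vs 25%.

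**After the fix.** With adherence taken only up to the first PU, the beta model gives 35.0% vs 34.8% at 35% risk (p<0.05 in 2.5% of runs) and 9.9% vs 9.9% at 10% risk (1.0%). This shows that the artefact comes from the period after the PU. It does not show that confounding is absent, because the model contains none.

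**The case against.** The document never says that a PU interrupts ES. The skin item on the stopping list concerns reactions during stimulation, and the bed-rest statement is general background. Nor does it say that adherence is totalled over the year: recording use for 12 months is not the same as summing it. Further process-evaluation detail is referred to Appendix 1, which is not shown and may set a window. All of this stands, and it is why the point is conditional.

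A reader might infer that a dose-response is bound to appear. The figures do not support that: the artefact is nil without interruption and small at 2 weeks, and at 10% risk it seldom reaches significance (10.9% of runs even at 8 weeks off).

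A reader might also infer that the plan will estimate treatment effects within groups defined by the timing, grade or location of PUs during the trial. The section on additional analyses only gives examples of what might be done and specifies no such model. Tabulating PUs by those features would be ordinary reporting.

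Finally, the aim is worded as exploratory and the text asks for careful conclusions. That limits the consequence. It does not answer the point, because the published text commits to the split, the regression and the curve, and the reason it gives for caution is a different one.

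**Conclusion.** The point holds conditionally. As written, the adherence analysis does not exclude ES use after the first PU. If PUs reduce later use, the comparison is biased towards an apparent benefit of adherence. With no true effect, the bias is modest at about 4 weeks off and material from about 8 weeks. At 35% risk and 8 weeks off, the odds ratio runs from 2.4 to 6.8 over the assumed adherence SDs. The size rests on assumptions that the documents do not supply: the mean and spread of adherence, the length of interruption and the median split. Only the secondary, exploratory adherence analysis is affected. The intention-to-treat primary analysis is not.

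**What to change.** In Process evaluation—mixed method analysis, state that adherence uses only ES use before the first PU, expressed as a rate and not a session total, since a total shrinks with time to PU.
- Preferred: ES use per fortnight as a time-updated exposure, lagged before each fortnightly PU report.
- Alternative: adherence in months 0–3 related to PUs after month 3.

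Adjust for number of previous PUs. Present the result and the curve as an exploratory, non-randomised association, and replace the sentence on differences between studies with one naming reverse causation and confounding.

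Under Methods for additional analyses {20b}, add only that the timing, grade and location of PUs during the trial are outcomes and will be reported as such if those optional analyses are done.

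The cost is wording: twice-monthly diaries and fortnightly PU reports are already planned. The landmark alternative loses PUs in the first three months; the time-updated form keeps them. Events will be few either way: 50 × 0.10 = 5 in the ES arm at the planned rate and 50 × 0.35 = 17.5 if ES does nothing. The estimate should therefore be shown with its interval and few covariates.
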